### Recruitment {15}

The research team recruited potential participants through face-to-face interactions at health services in the two cities, as well as phone calls to individuals listed in a database from previous studies conducted by the research group [38, 41, 42], none of which involved exercise or educational interventions. In addition, social media advertisements were utilized, and the study was disseminated among local healthcare providers through face-to-face interactions and via email among employees of the Federal University of Juiz de Fora (UFJF) and the Federal University of Minas Gerais (UFMG), respectively.

## Assignment of interventions: allocation

### Sequence generation {16a}

A block random assignment sequence was generated with a 1:1 ratio, using the website www.randomization.com by assigning enrolled individuals to one of the two study arms in each research center.

### Concealment mechanism {16b}

The principal investigator maintained an allocation sequence for each center in two separate password-protected files. It was shared with the research center coordinators, who distributed the allocated program to the intervention team members only after conducting theparticipants’ baseline assessment. This allocation information will not be accessible to the outcome assessors to ensure allocation concealment. 

### Implementation {16c}

After the baseline assessment, the center research coordinator received the participant’s allocation from the principal investigator. The allocation was disclosed to the participant and the intervention team members, but it remains concealed from the outcome assessors, who are blinded to the allocated intervention.

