#### Secondary outcomes

The secondary outcomes are divided in health behaviors (health literacy [39], physical activity level [40], exercise self-efficacy [41], adherence to Mediterranean diet [42], and medication adherence [43]) and cardiometabolic health parameters (glycemic control [44], anthropometric characteristics, and cardiac autonomic control [45]), as described in Table 2.

**Table 2 Tab2:** Description of the secondary outcomes

Secondary outcomes	Measurement tools	Measurement description/range
Health literacy	NVS health literacy instrument	Total score ranging from 0 (no health literacy) to 6 (highest health literacy)
Physical activity level	Steps	Total steps/week and average of steps/day obtained from daily steps number for seven days measured by a pedometer
Exercise self-efficacy	Brazilian Portuguese version of BESES	Total score ranging from 0 (not confident) to 100 (completely confident)
Adherence to Mediterranean diet	Brazilian Portuguese version of the MDS	Total score ranging from 0 (no adherence) to 13 (highest adherence to Mediterranean food pattern)
Medication adherence	Brazilian version of the MAT ADOs and MAT insulin	Total score ranging from 0 (no adherence) to 7 (highest medication adherence)
Glycemic control	Results from A1c exams	Routine laboratory tests dated no longer than 3 months before the study assessment point
Anthropometric characteristics	BMI and waist circumference	Weight (kg) and height (m) measured to calculate BMI (kg/m^2^), waist circumference (cm) measured at the superior border of the iliac crest
Cardiac autonomic control	Five-minute resting HRV	SDNN (ms), RMSSD (ms), pNN50 (%), SD1 (ms), SD2 (ms), SD1/SD2 ratio, LF (ms^2^), HF (ms^2^), LF (nu), HF (nu), LF/HF ratio, TP (ms^2^)

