*Abbreviations*: *NVS* Newest Vital Sign, *BESES* Bandura's Exercise Self-Efficacy Scale, *MDS* Mediterranean Diet Scale, *MAT ADOs* Brazilian version of the Measure of Adherence to Oral Antidiabetic, *MAT* insulin Insulin Treatments questionnaire, *A1c* glycated hemoglobin, *BMI* Body Mass Index, *HRV* Heart Rate Variability, *iNN* normal RR intervals, *ms* milissegundos, *SDNN* Standard deviation of iNN, *RMSSD* root mean square of the differences between successive iNN, *pNN50* percentage of successive iNN with a duration difference greater than 50ms, *SD1* Poincaré plot standard deviation perpendicular the line of identity, *SD2* Poincaré plot standard deviation along the line of identity, *LF* low-frequency spectral components, *HF* high-frequency spectral components,  *ms²* spectral components in absolute units, *nu*  spectral components in normalized units, *TP* total power

Health literacy, exercise self-efficacy, adherence to the Mediterranean diet, medication adherence, and all cardiometabolic health parameters will be measured during both the baseline and outcomes assessment appointments. Physical activity levels will be measured (1) over the 7 days following the baseline assessment appointment; (2) over the 7 days leading up to the post-intervention assessment appointment; and (3) over the 7 days following the post-follow-up assessment appointment or seven days leading up to this appointment to those participants who kept with them the pedometer worn in the past outcome assessment appointment.

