
### Participant timeline {13}

All assessment appointments will be scheduled individually, based on participants’ and research team members’ schedules.

After attending the baseline assessment appointment, the participant will be wearing a pedometer for 7 days before starting the intervention. To accommodate all participants enrolled at that time into the timetable of baseline assessment appointment and have their physical activity level measured before the intervention gets started, a period of up to 21 days including the 7-day wearing a pedometer will be allowed between the baseline assessment appointment and the first intervention session. Therefore, the baseline assessment could be carried out between one and 14 days previous to the first intervention session.

After the intervention conclusion, the participant will be wearing a pedometer for 7 days before attending the post-intervention assessment appointment. To accommodate all participants into the post-intervention assessment appointment timetable and have their physical activity level measured before this appointment, a period of up to 21 days including the 7-day wearing a pedometer will be allowed between the intervention conclusion and post-intervention assessment appointment. Therefore, the post-intervention assessment could be carried out between 7 and 21 days after the intervention conclusion.

Upon completing the 6-month follow-up, the participant will be wearing a pedometer for 7 days: (1) after attending the post-follow-up assessment appointment when this appointment is scheduled between 1 and 14 days after the 6-month follow-up completion or (2) before attending the post-follow-up assessment appointment when this appointment is scheduled between 7 and 21 days after 6-month follow-up completion. To accommodate all participants into the post-follow-up assessment appointment schedule and have their physical activity level measured after 6-month follow-up completion, a period of up to 21 days including the 7-day wearing a pedometer will be allowed between the 6-month follow-up completion and post-follow-up assessment appointment. Therefore, the post-follow-up assessment could be carried out between 1 and 14 days after the 6-month follow-up completion.

Table 3 shows the participant timeline.

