## Assignment of interventions: blinding

### Who will be blinded {17a}

Due to the nature of the intervention, participants and the intervention team members cannot be blinded to the allocation. However, to ensure objectivity, two independent research team members, blinded to the allocation, will handle database management and conduct statistical analyses, respectively.

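### As written, unblinded participants may know their arm during the week in which baseline steps are recorded; the protocol should say when disclosure took place and add two sensitivity analyses for this secondary outcome.

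*Protocol article*

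**What the plan says.** Three parts of the protocol article bear on this.

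**Release of the arm.** Implementation {16c}: "After the baseline assessment, the center research coordinator received the participant’s allocation from the principal investigator". The same section goes on: "The allocation was disclosed to the participant and the intervention team members, but it remains concealed from the outcome assessors". Concealment mechanism {16b} likewise lets the coordinators pass the allocation on only once the participant's baseline assessment has been done. Neither section gives a disclosure date or mentions the pedometer.

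**Timing of the baseline measures.** Under Secondary outcomes, most measures are taken at the visit; for example, "all cardiometabolic health parameters will be measured during both the baseline and outcomes assessment appointments". Physical activity is the exception: "Physical activity levels will be measured (1) over the 7 days following the baseline assessment appointment". Participant timeline {13} agrees: "After attending the baseline assessment appointment, the participant will be wearing a pedometer for 7 days before starting the intervention". Table 2 defines the outcome as "Total steps/week and average of steps/day obtained from daily steps number for seven days measured by a pedometer".

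**Blinding and analysis.** Who will be blinded {17a} says that "participants and the intervention team members cannot be blinded to the allocation". The statistical methods section compares baseline with post-intervention between groups by a 2 × 2 ANOVA.

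**The concern.** A baseline value is safe from the assigned arm only if it is recorded before the participant learns the arm. Measures taken at the baseline appointment meet that condition. Steps are recorded afterwards, and the release of the allocation is not tied to the end of the recording.

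Blinded assessors and analysts do not help, because the wearer produces the count and can change it by walking more or less. If learning of the added education classes changes walking in one arm and not the other, the step baseline carries part of the arm's effect, and the ANOVA subtracts it from the result. What is at stake is the between-arm estimate for one secondary outcome.

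This is separate from whether the pedometer week can overlap the first intervention sessions. The problem would exist even if all seven days came before the first session.

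**Working it through.** The protocol states no figure to reproduce here. The check covers the order of events, then the algebra of the bias, then the precision cost of the alternative analysis.

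**1. Order of events**

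| Event | Timing given | Where |
|---|---|---|
| ISWT, DATE-Q and most secondary outcomes | at the baseline appointment | Primary outcomes; Secondary outcomes |
| Baseline steps | 7 days after the appointment | Secondary outcomes; Participant timeline {13} |
| Allocation to coordinator, then participant | after the baseline assessment, no date | {16b}, {16c} |

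Whether the third row can precede or overlap the second depends on what *baseline assessment* means.

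- *The visit only.* Eligibility criteria {10} invites people to the baseline assessment and confirms eligibility there before data collection starts, which describes a visit. On this meaning, disclosure before or during the pedometer week is allowed.
- *The visit plus the pedometer week.* The Table 3 footnote describes t0 as a 1 to 21-day interval for the baseline assessment, and Participant timeline {13} counts the 7 pedometer days within its 21 days. On this meaning, release comes after the steps are recorded and there is no problem.

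The 1 to 14-day statement in Participant timeline {13} does not settle the matter. It does not fit the 21-day allowance in the same paragraph if it refers to the visit, and 21 − 7 = 14 could point to the second meaning. The text is therefore ambiguous.

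**2. Bias if the arm is known**

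Let D be the true effect on post-intervention steps. Let a_E and a_C be the shifts in baseline steps caused by knowing the arm (ExLE and Ex), and let x = a_E − a_C. With complete data, the group-by-time term is

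(post_E − base_E) − (post_C − base_C) = D − x.

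A reaction shared by both arms gives x = 0 and cancels. For a differential reaction, x has to be assumed. A simulation with no true effect (400,000 simulated participants, baseline-to-post correlation ρ of 0.5 or 0.7) gave:

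| Assumed x (SD) | Bias of contrast, ρ = 0.5 | Bias of contrast, ρ = 0.7 |
|---|---|---|
| 0.1 | −0.101 | −0.096 |
| 0.2 | −0.196 | −0.201 |
| 0.3 | −0.302 | −0.301 |

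These agree with −x. If x has the opposite sign, so does the bias. Adjusting for the affected baseline, which the protocol does not plan, would leave −ρx: about −0.05 to −0.15 SD at ρ = 0.5 and −0.07 to −0.21 SD at ρ = 0.7.

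**3. Precision of a comparison without the step baseline**

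With equal variance σ² at both times and n per arm, the variance of the between-arm difference is:

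- post-intervention only: 2σ²/n
- change from baseline: 4σ²(1 − ρ)/n
- baseline-adjusted: 2σ²(1 − ρ²)/n

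Post-only against change is 1/[2(1 − ρ)]: 1.00 at ρ = 0.5 and 1/0.6 = 1.67 at ρ = 0.7. Post-only against baseline-adjusted is 1/(1 − ρ²): 1/0.75 = 1.33 and 1/0.51 = 1.96. Both values of ρ are assumptions.

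**The case against.** The strongest defence is that the article does not say that disclosure came first. It ties release to the baseline assessment, whereas the visit is elsewhere called the baseline assessment appointment, so the pedometer week may be included. The day on which a participant is told the arm is also an operational detail that the full protocol or the team's manuals may fix. This stands in part. A reader might infer that baseline steps were recorded after disclosure as a rule, and the article does not support that. It does state both the release trigger and the pedometer timing, however, and together they leave the order open.

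The second defence is that both arms are about to start the same exercise programme with the same counselling, so most anticipation should be shared and cancel. This stands. Only a differential reaction to the added classes matters.

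A reader might also infer that the bias works against ExLE, because participants allocated to it become more active early or those allocated to Ex lose heart. The documents do not support a direction: Ex participants who walked more to compensate would push the estimate the other way.

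The last defence is that dropping the step baseline from the main analysis would be disproportionate to a bias not shown to exist. This also stands, given a variance up to 1.67 times that of the planned contrast at ρ = 0.7.

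**Conclusion.** The point holds in a limited form. As written, the protocol allows unblinded participants to know their arm during the baseline pedometer week. Any differential reaction x would enter the group-by-time contrast for steps as −x. Whether disclosure came first, and whether x differs from zero, cannot be told from the article. The 0.1 to 0.3 SD range illustrates how the bias scales and is not an estimate.

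The scope is one secondary outcome. ISWT distance and DATE-Q are measured at the appointment, so nothing here reaches the primary outcomes or the sample size. Severity is minor.

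**What to change.** 1. In Concealment mechanism {16b} and Implementation {16c}, state whether participants learned their arm before or after the baseline pedometer week, using disclosure and wear dates where they were recorded. Recruitment ended in February 2024, so this reports what was done; a new rule could no longer change conduct. If disclosure always waited, one sentence closes the point.
2. Keep the planned analysis for steps.
3. Pre-specify two sensitivity analyses before the data are analysed:
   - (a) a between-arm comparison of post-intervention steps without the step baseline. Randomisation protects it from this problem, and it needs no disclosure dates.
   - (b) where dates exist, the baseline-based analysis using only step baselines completed before disclosure.
4. State in advance that, if the dates show that disclosure commonly came before the pedometer week, the step result will be interpreted from (a).

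The cost is a wording change, a date check per participant where records exist, and a little extra analysis. Both sensitivity analyses may be less precise: (a) by the variance ratios shown above, and (b) because it uses fewer participants. The article does not say that disclosure dates were kept. If they were not, (b) cannot be run and (a) stands alone.

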## Assignment of interventions: blinding

### Who will be blinded {17a}

Due to the nature of the intervention, participants and the intervention team members cannot be blinded to the allocation. However, to ensure objectivity, two independent research team members, blinded to the allocation, will handle database management and conduct statistical analyses, respectively.

### Procedure for unblinding if needed {17b}

Given that the trial does not involve drug testing, there will be no need for emergency unblinding.

## Data collection and management

### Plans for assessment and collection of outcomes {18a}

All research team members will receive training specific to their assigned responsibilities in the research, whether it involves conducting baseline assessments or outcome assessments. Additionally, they will adhere to a research-specific manual tailored to their respective roles to ensure that all procedures are carried out in accordance with the validation of assessment tools or any necessary training, especially for tools developed by the research team.

### Plans to promote participant retention and complete follow-up {18b}

There are no plans to promote participant retention. To minimize dropouts on the 6-month follow-up, the participants will receive monthly phone calls to remind them about filling out the diabetes-related morbidity tool and the post-follow-up assessment appointment.

### Data management {19}

All trial data will be entered into an Excel file by an independent research team member who is not an intervention team member, outcome assessor, or data analyst. Additionally, 30% of the entered data will be randomly checked by one of the research center coordinators.

### Confidentiality {27}

The collected data will be anonymized using individual participants’ coding to label the trial data. The link between identifiable personal data and the codes will be stored securely and separately from the trial data.

### Plans for collection, laboratory evaluation, and storage of biological specimens for genetic or molecular analysis in this trial/future use {33}

No biological specimens will be collected in this trial.

## Statistical methods

### Statistical methods for primary and secondary outcomes {20a}

The participants’ characteristics will be presented as central tendency and dispersion measures or absolute values and percentages. These data will be compared using the independent *t*-test for continuous variables and chi-square or Fischer’s exact test for categorical variables.

#### Primary and secondary outcomes

Primary and secondary outcomes will be presented as central tendency and dispersion measures. Data distribution will be analyzed using the Shapiro–Wilk test. The analysis of variance (2 × 2 ANOVA) will compare data between baseline and post-intervention and between groups. An alpha of 5% will be considered for statistical significance, and post hoc comparisons will be performed to detect two-by-two differences. In case of missing data, the statistical procedures will follow the intention to treat.

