**Methods:**

Multicenter double-blinded randomized controlled trial with two parallel arms involving 12-week intervention and 6-month follow-up. The eligible individuals (≥ 18 years, living with prediabetes or diabetes, literate, no clinical decompensation and/or physical and/or mental limitations that contraindicate physical exercising, written physician permission for exercise, no cognitive impairment, no vision limitations for reading, no confirmed diagnosis of unstable coronary disease or heart failure, no pacemaker and/or implantable cardioverter-defibrillator, no complex ventricular arrhythmias, no intermittent claudication, no recent cardiovascular event or cardiac surgery, and no currently enrolled in a structured exercise program) were recruited from two Brazilian cities and randomized to either (1) an Exercise and Lifestyle Education Program (ExLE) or (2) an Exercise Program (Ex), which can be delivered on-site or remotely based on the participants’ internet access and technology literacy. The primary outcomes will be changes in functional capacity and disease-related knowledge. The secondary outcomes will involve changes in health behaviors (health literacy, physical activity level, exercise self-efficacy, and medication adherence) and cardiometabolic health parameters (glycemic control, anthropometric measures, and cardiac autonomic control). Program adherence, satisfaction with the program, diabetes-related morbidity, and changes in quality of life, depression, and diet quality will be the tertiary outcomes. Assessments will occur at baseline, post-intervention, and after 6-month follow-up.

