### Outcomes {12}

#### Primary outcomes

The primary outcomes of this study will include functional capacity and disease-related knowledge. Functional capacity will be measured by the distance covered in meters during the incremental shuttle walk test (ISWT) [37], while disease-related knowledge will be assessed using the total score of the Brazilian Portuguese version of the DiAbeTes Education Questionnaire (DATE-Q) [38]. The DATE-Q total score, ranging from 0 (indicating no disease-related knowledge) to 20 (indicating the highest level of disease-related knowledge) is obtained by a 20-item questionnaire with response options of true/false/do-not-know. The primary outcomes will be measured during baseline and outcomes assessment appointments.

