### Sample size {14}

The sample size was calculated considering the ISWT distance as the primary outcome, using parameters derived from a previous study involving educational intervention in cardiac rehabilitation [50]. The calculation was performed using R Software version 3.4.3, with the following parameters: a moderate effect size (*d* = 0.20), 80% statistical power, a 5% alpha level, one-sided test, two arms, and three measurements. A total sample size of 200 participants (100 per arm) was determined. Assuming a 20% attrition rate, based on a previous study [50], 120 participants would be enrolled in each arm to ensure that 200 participants complete the study protocol.

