#### Tertiary outcomes

Quality of life, depression, and diet quality will be presented and analyzed as the primary and secondary outcomes. Data from the program adherence and morbidity associated with diabetes will be analyzed using the independent *t*-test. Regarding satisfaction with the program, it will be analyzed descriptively from absolute values and percentages.

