## Abbreviations

LMIC: Low- and middle-income countries
HIC: High-income countries
RCT: Randomized clinical trial
ExLE: Exercise and Lifestyle Education Program
Ex: Exercise Program
FFQ: Food frequency questionnaire
HRV: Heart rate variability
GEE: Generalized estimation equations
ISWT: Incremental shuttle walking test
DATE-Q: DiAbeTes Education Questionnaire
NVS: Newest vital sign
MDS: Mediterranean Diet Scale
SF-36: Medical Outcomes Study 36-Item Short-Form Health Survey
BESES: Bandura’s exercise self-efficacy scale
MAT ADOs and MAT insulin: Measure of Adherence to Oral Antidiabetic and Insulin Treatments questionnaire
A1c: Glycated hemoglobin
BMI: Body mass index
iNN: Normal RR intervals
SDNN: Standard deviation of normal RR intervals
RMSSD: Root mean square of the differences between successive normal RR intervals
pNN50: Percentage of successive normal RR intervals with a duration difference greater than 50 ms
SD1: Poincaré plot standard deviation perpendicular the line of identity
SD2: Poincaré plot standard deviation along the line of identity
LF: Low-frequency spectral component
HF: High-frequency spectral component
TP: Total power

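### The stated ANOVA stops at the post-intervention visit, so no between-arm test of the 6-month values is specified, although the trial is scheduled and sized for three measurements

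*Protocol article*

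**What the plan says.** **Schedule.** The Abstract of the protocol article gives three assessments: "Assessments will occur at baseline, post-intervention, and after 6-month follow-up". Under Outcomes, the text on functional capacity (ISWT) and disease knowledge (DATE-Q) says: "The primary outcomes will be measured during baseline and outcomes assessment appointments". The secondary outcomes other than physical activity "will be measured during both the baseline and outcomes assessment appointments". Pedometer steps have an explicit third measurement, either "over the 7 days following the post-follow-up assessment appointment" or in the week before that appointment.

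**Sample size {14}.** The calculation is for ISWT distance and assumes a "one-sided test, two arms, and three measurements".

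**Statistical methods {20a}.** For primary and secondary outcomes: "The analysis of variance (2 × 2 ANOVA) will compare data between baseline and post-intervention and between groups". For three tertiary outcomes: "Quality of life, depression, and diet quality will be presented and analyzed as the primary and secondary outcomes". Diabetes-related morbidity, collected over the 6-month follow-up, is to be compared with an independent t-test. The only additional analysis, under {20b}, is an interaction with delivery mode.

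**The concern.** The article does more than leave the longitudinal analysis open for a later plan. It fixes a model and names its two time points, and these do not match the three assessments in its own design or the three measurements in its own sample size.

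If the text is followed, the results will contain no specified test or interval for the arm difference at 6 months in walking distance, knowledge, health behaviours, cardiometabolic measures, quality of life, depression or diet quality. A reader could not tell from the plan whether a 6-month comparison that appears in the report was intended, or what standing it has beside the post-intervention result. With two primary outcomes and two post-baseline visits, that status should be settled in advance.

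**Working it through.** The point is a comparison of passages. The arithmetic only shows its extent.

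**1. Visits scheduled and visits tested**

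| Outcome | Third assessment scheduled in | Between-arm test stated | 6-month values in that test? |
|---|---|---|---|
| ISWT, DATE-Q | Abstract; Primary outcomes | 2 × 2 ANOVA | No |
| Secondary outcomes | Abstract; Secondary outcomes | 2 × 2 ANOVA | No |
| Quality of life, depression, diet quality | Abstract (general statement) | 2 × 2 ANOVA, by reference | No |
| Diabetes-related morbidity | Tertiary outcomes (over the follow-up) | Independent t-test | Yes |

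For the third row the Outcomes section gives no separate timing, and Table 3 is not readable in the copy reviewed. That row rests on the Abstract's general statement.

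**2. Cells**

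- Design: 2 arms × 3 assessments = 6 cells.
- Stated ANOVA: 2 × 2 = 4 cells. The two 6-month cells are left out.
- Arm-by-time degrees of freedom: (2−1)(2−1) = 1 as stated, and (2−1)(3−1) = 2 with three measurements.
- The post hoc comparisons belong to the same model, so they cannot reach a visit outside it.

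**3. People affected**

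Enrolment is 120 per arm, 240 in all. With the assumed 20% attrition, 240 × 0.8 = 192 would be expected to supply 6-month values.

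**4. Can the sample size of 200 show which design was meant?**

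Stated inputs: d = 0.20, power 80%, alpha 5%, one-sided, two arms, three measurements, N = 200. The correlation between measurements is not given.

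- Simple two-sample comparison, one-sided: n per arm = 2(1.645 + 0.842)² / 0.20² ≈ 309.3, so 310 per arm. The 200 does not come from this.
- Arm-by-time F test at alpha 0.05, with d = 0.20 taken as f = d/2 = 0.10, noncentrality λ = f²·N·m/(1−ρ), and m−1 and (N−2)(m−1) degrees of freedom:

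| Assumed ρ | Total N, m = 2 | Total N, m = 3 |
|---|---|---|
| 0 | 395 | 323 |
| 0.3 | 277 | 227 |
| 0.5 | 199 | 163 |
| 0.7 | 120 | 98 |

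At N = 199, m = 2, ρ = 0.5: λ = 0.01 × 199 × 2 / 0.5 = 7.96. At N = 163, m = 3, ρ = 0.5: λ = 0.01 × 163 × 3 / 0.5 = 9.78.

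- Reading 0.20 itself as f, a 1-df between-arm F test with λ = f²·N gives N = 199 (λ = 0.04 × 199 = 7.96).

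A total near 200 can thus be reached with two measurements at ρ = 0.5, with three at some ρ between 0.3 and 0.5, or by treating d as f. The 200 cannot be reproduced uniquely, so it neither confirms nor refutes the 2 × 2 analysis. What the table does show is that the number of measurements changes the required N: 199 against 163 at ρ = 0.5. The sample-size basis and the analysis should therefore name the same design.

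**The case against.** The case on the other side has real weight.

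- **The main comparison survives.** The hypothesis that the combined programme beats exercise alone can be tested at post-intervention, and the stated ANOVA names that visit. This stands: the omission neither biases nor removes that comparison.
- **Never analysed would be too strong.** A reader might infer that the 6-month data are collected and then ignored. The article plans descriptive summaries of primary and secondary outcomes without limiting them to particular visits, morbidity has a test, and a full protocol or analysis plan not shown could add a model. What holds is that this article specifies no inferential between-arm analysis of the 6-month values other than for morbidity.
- **Maintenance is not a stated purpose.** A reader might assume that the follow-up exists to show lasting benefit. The Objectives and the Discussion attach six months only to diabetes morbidity, which has a test. The failure of a declared maintenance aim cannot be claimed.
- **A later 6-month analysis need not be post hoc.** Naming post-intervention fixes the inferential time point as the text stands, and a contrast added before the analyst sees data by arm would still be pre-specified. This is correct, and it is why the date of the change matters.
- **The abbreviation list proves nothing.** "GEE: Generalized estimation equations" appears there and not in the methods shown. It may be a leftover, or a trace of a longitudinal method in the full protocol.
- **Zero imputation is separate.** A reader might suppose that the ANOVA's need for complete pairs led to the rule of entering zero for missing values. The article ties that rule to intention to treat and gives no such reason.

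None of this removes the conflict between a two-visit test and a design and sample size built on three.

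**Conclusion.** The point holds in a limited form. The article restricts its only inferential method for the primary and secondary outcomes, and for quality of life, depression and diet quality, to baseline and post-intervention. The same outcomes are scheduled again after the 6-month follow-up, and the trial was sized for three measurements.

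Its extent is one of three scheduled visits, one of the two post-baseline visits, and two of six design cells, for about 192 expected completers. Morbidity is not affected.

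This rests on two readings: that the outcomes assessment appointments include the post-follow-up one, as the Abstract indicates, and that the Abstract's schedule covers the three tertiary scores. It does not depend on how the 200 was obtained. It is a specification conflict that governs both primary outcomes and should be settled before analysis; it is not a flaw that invalidates the post-intervention result.

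**What to change.** In Statistical methods {20a}, replace the 2 × 2 ANOVA with one longitudinal model per outcome, either a mixed model for repeated measures or GEE:

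- terms: arm, visit (post-intervention, 6 months), arm × visit, and the baseline value of the outcome;
- primary contrast: the arm difference at post-intervention, with a 95% CI;
- pre-specified secondary contrast: the arm difference at 6 months, with a 95% CI;
- the same model for quality of life, depression and diet quality, so that the cross-reference under Tertiary outcomes still works.

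In Sample size {14}, state which contrast the calculation supports and the correlation it assumed, so that the three measurements there match the analysis.

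Date the change before the blinded analyst sees outcome data by arm. The Trial status section expects data collection to end by December 2024 and closure in May 2025 after analysis. If that point has already passed, the 6-month contrast should be reported as added later.

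A lesser remedy is to keep the two-visit test and say outright that 6-month values are descriptive only. That would reconcile the text but give no estimate of the arm difference from data already being collected. The fuller change needs no new data, only revised wording and slightly more analysis work.
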